# Study protocol: safety and efficacy of propranolol 0.2% eye drops in newborns with a precocious stage of retinopathy of prematurity (DROP-ROP-0.2%): a multicenter, open-label, single arm, phase II trial

**DOI:** 10.1186/s12887-017-0923-8

**Published:** 2017-07-14

**Keywords:** Propranolol, Beta blocker, Proliferative retinopathy, Angiogenesis

## Abstract

**Background:**

Retinopathy of prematurity (ROP) still represents one of the leading causes of visual impairment in childhood. Systemic propranolol has proven to be effective in reducing ROP progression in preterm newborns, although safety was not sufficiently guaranteed. On the contrary, topical treatment with propranolol eye micro-drops at a concentration of 0.1% had an optimal safety profile in preterm newborns with ROP, but was not sufficiently effective in reducing the disease progression if administered at an advanced stage (during stage 2). The aim of the present protocol is to evaluate the safety and efficacy of propranolol 0.2% eye micro-drops in preterm newborns at a more precocious stage of ROP (stage 1).

**Methods:**

A multicenter, open-label, phase II, clinical trial, planned according to the Simon optimal two-stage design, will be performed to analyze the safety and efficacy of propranolol 0.2% eye micro-drops in preterm newborns with stage 1 ROP. Preterm newborns with a gestational age of 23–32 weeks, with a stage 1 ROP will receive propranolol 0.2% eye micro-drops treatment until retinal vascularization has been completed, but for no longer than 90 days. Hemodynamic and respiratory parameters will be continuously monitored. Blood samplings checking metabolic, renal and liver functions, as well as electrocardiogram and echocardiogram, will be periodically performed to investigate treatment safety. Additionally, propranolol plasma levels will be measured at the steady state, on the 10th day of treatment. To assess the efficacy of topical treatment, the ROP progression from stage 1 ROP to stage 2 or 3 with plus will be evaluated by serial ophthalmologic examinations.

**Discussion:**

Propranolol eye micro-drops could represent an ideal strategy in counteracting ROP, because it is definitely safer than oral administration, inexpensive and an easily affordable treatment. Establishing the optimal dosage and treatment schedule is to date a crucial issue.

**Trial registration:**

ClinicalTrials.gov Identifier NCT02504944, registered on July 19, 2015, updated July 12, 2016. EudraCT Number 2014–005472-29.

**Electronic supplementary material:**

The online version of this article (doi:10.1186/s12887-017-0923-8) contains supplementary material, which is available to authorized users.

## Background

### Background and rationale

Retinopathy of prematurity (ROP) is a potentially blinding disease caused by pathologic angiogenesis that occurs in the incompletely vascularized retina of preterm newborns. Despite current therapeutic strategies, ROP still represents a leading cause of potentially avoidable visual impairment and blindness in childhood. More than 30,000 preterm infants become blind or visually impaired from ROP each year worldwide [1]. In the 1940s, the so-called “first ROP epidemic” was related to the widespread use of unrestricted oxygen supplementation; the second “ROP epidemic” occurred in high-income countries in the 1970s and it was related to the increasing survival rate at lower gestational age (GA) [2–4]. In the early 1990s, an emerging epidemic of blindness due to ROP was also recorded in middle-income countries [5]. Currently, Asia is the region presenting the highest incidence of blindness due to ROP, followed by Latin America, where some countries account for an incidence of blindness/severe visual impairment related to ROP that is 2.4 times higher than in highly industrialized countries [1, 6, 7]. Therefore, the detection of a new inexpensive and easily affordable treatment strategy may be a relevant issue of global interest. Prematurity and low birth weight are the main factors associated with ROP, although other factors (i.e. respiratory failure, fetal hemorrhage, intra-ventricular hemorrhage, blood transfusions, hyperglycemia, sepsis, necrotizing enterocolitis) have been described as contributing factors to ROP development [8, 9].

Physiologically, retinal blood vessels development begins at the optic disc during the fourth month of gestation in the hypoxic uterine environment and is completed at approximately 40 weeks of gestational age. The pathogenesis of ROP has not yet been totally clarified, but the most validated hypothesis describes two different postnatal phases [10]. During the first phase, the loss of the placenta and the exposure to extrauterine relative hyperoxia are associated with low levels of Vascular Endothelial Growth Factor (VEGF) and Insulin-like Growth Factor 1 (IGF-1), resulting in a cessation of retinal vascularization [11–14]. In fact, oxygen induces retinal vasoconstriction, prevents retinal vessel growth and therefore still represents one of the main determinant of ROP development [15]. During the second phase, the retinal maturation and the development of relative hypoxia stimulate the VEGF and IGF-1 expression, causing a shift to a proliferative phase, which is characterized by an abnormal angiogenesis [16–18].

For a long time an oxygen saturation level lower than 90% has been suggested to reduce ROP risk. However, the recent demonstration that a higher oxygen saturation (91–95%) correlates with an improved survival represents an actual dilemma because, unfortunately, it induces a higher risk of ROP development [15]. Apart from oxygen tension, which is the main factor promoting the expression of angiogenic growth factors in proliferative retinopathies, other mechanisms are involved in the vascular response to ischemia/hypoxia, including the activation of inflammatory signaling pathways, oxidative stress and the production of nitric oxide [19]. Genetic factors might also affect the risk for ROP, even though no one has been identified thus far. The disease progresses more often in white than black infants and in boys than girls [20, 21].

#### The role of the β-adrenergic system

Propranolol is a non-selective β-adrenoreceptor (β-AR) antagonist. For many years, it has been largely used in the pediatric population affected by cardiovascular diseases (i.e. arterial hypertension, obstructive hypertrophic cardiomyopathy, Fallot tetralogy and arrhythmia), hyperthyroidism (i.e. neonatal thyrotoxicosis), migraine and portal hypertension with gastroesophageal varices at risk of bleeding. Propranolol is also effective and sufficiently safe in treating infantile hemangioma (IH) in childhood [22–24] and the European Medicines Agency (EMA) has recently authorized the use of propranolol for life-threatening IH, at risk of ulceration or permanent deformation. The working mechanisms of propranolol in reducing proliferative IH are not completely known and include vasoconstriction, induction of epithelial cells apoptosis and inhibition of angiogenesis [25–27]. The growth of IH is enhanced by pro-angiogenic factors, including VEGF and basic fibroblast growth factor (bFGF) and propranolol inhibits the growth of IH by decreasing the expression of pro-angiogenic factors and Hypoxia Inducible Factor 1 (HIF-1) induced by adrenergic receptors [26–32]. Some pathogenic aspects of ROP are probably common to IH, as suggested by the evidence that ROP and IH often coexist in infants weighting <1250 g [33] and that both diseases share the same histological feature. For instance, endothelia of IH and of retinal neovasculature in ROP express GLUT1 [34, 35], a factor significantly up-regulated in hypoxic tissues and stimulated by HIF-1 [36].

Additionally, as for IH, the vascular proliferative phase induced by hypoxia, which is the “second phase” in ROP pathogenesis, is promoted by VEGF. Considering that both β1 and β2-ARs are expressed in the retina [37–40], that hypoxia increases VEGF levels presumably through overactivation of the β-adrenergic system as suggested by norepinephrine accumulation in response to hypoxia [41, 42], that β-AR blockade is effective in mouse models of retinal neovascular diseases, our assumption was that the use of β-AR blockers, such as propranolol, could be useful for the treatment of ROP in infants. Indeed, several studies using a mouse model of oxygen-induced retinopathy (OIR) [43, 44] have analyzed the role of the adrenergic system in the ROP pathogenesis and the effects of β-AR antagonists and agonists on ROP development [45–47]. These studies confirmed that retinal exposure to hypoxia leads to an increase in catecholamine release, which promotes the up-regulation of pro-angiogenic factors and retinal angiogenesis by over-activating β-ARs [46]. The β-AR blockade by systemic propranolol administration decreases VEGF and IGF-1 levels, retinal hemorrhage, retinal tufts and blood-retinal barrier breakdown, improving the retinopathy score [45]. Similar findings were observed using selective β2-AR blockade [47] and after β2-AR desensitization following agonist administration [46], confirming that β2-ARs play a central role in the pathogenesis of ROP.

However, these findings obtained in C57BL/6 mice seem to conflict with results reported in 129S6 mice, a strain predisposed to develop a more aggressive neovascularization [48] and characterized by an impressive up-regulation of β3-ARs [49]. In this strain propranolol does not seem to affect the retinal response to hypoxia [49], but our hypothesis was that probably the different genetic background of the mouse strain might contribute to the different retinal responses to hypoxia [50]. The hypothesis that the insensitivity to propranolol of 129S6 mice was due to the preponderance in this strain of β3-ARs, that are minimally blocked by propranolol [51], was confirmed by the discovery that this receptor is involved in VEGF production in hypoxic retinas, through the nitric oxide pathway [52]. The discovery of a proangiogenic action of β3-ARs suggested to investigate a possible role for this receptor also in cancer growth [53–55], a new frontier of research currently for neonatologists.

#### Efficacy and safety of oral propranolol

The studies in the OIR model provided a considerable amount of results which strongly indicate that β2-AR blockade may play a significant action against hypoxia-induced retinal neovascularization. This evidence prompted an interest in exploring the possibility that the administration of propranolol may not only be used to treat IH but also be of help in the treatment of ROP. A randomized controlled trial [56] was performed to verify the efficacy and safety of oral propranolol in preterm newborns (GA < 32 weeks) with ROP stage 2 without plus in zone II [57]. Oral propranolol significantly decreased ROP progression to both stage 3 and stage 3 with plus, and none of treated newborns progressed to stage 4. The number of newborns who underwent laser photocoagulation or bevacizumab administration was significantly lower in the treated group [56]. These data are consistent with those reported by other authors [58–60]. Despite propranolol being generally safe and well tolerated in infancy, serious adverse events have been reported in unstable preterm newborns, mainly in conjunction with other conditions, such as sepsis, anesthesia or tracheal stimulation [56]. In these patients receiving the lower dose of 1 mg/kg/day, mean propranolol plasma concentration was around 20 ng/mL. Considering that pharmacological effects of β-blockers are usually related to the plasma concentrations, it appears prudent to avoid in future clinical trials propranolol concentrations higher than 20 ng/mL, that was considered a sort of safe cut-off value [56]. Although propranolol is effective in counteracting ROP progression [56, 58–60], the incidence of adverse events indicates that systemic administration is not sufficiently safe in preterm newborns [56]. Recently, also prophylactic propranolol administered on seventh day of life showed a decreasing trend in the incidence of ROP, need for laser therapy, and treatment with anti-VEGF [61].

#### Efficacy of propranolol eye drops in animal models

Since the oral administration of propranolol did not guarantee adequate safety, further experiments investigated the efficacy and safety of topical propranolol, in the form of eye drops, in animal models. In 2013, Dal Monte and co-workers demonstrated that 2% topical propranolol administration provides the retina with a drug concentration that are adequate to decrease pro-angiogenic factors (VEGF and IGF-1), retinal angiogenesis and blood-retinal barrier breakdown in OIR mice [62]. The efficacy and safety of topical propranolol were also evaluated in a rabbit model [63]. Male New Zealand white rabbits were treated with propranolol-based ocular drops at 0.1% of concentration, applied every 6 h to both eyes for 5 days. Retinal and plasma concentrations of propranolol were measured and compared with those registered after oral treatment. Despite retinal drug concentrations being similar to those reported after oral treatment, plasma propranolol levels were significantly lower after topical administration. Additionally, Draize test (a classical acute toxicity test) and cornea’s histological analysis showed no significant differences between control and treated eyes, confirming that local tolerability of ocular propranolol drops was optimal. All these findings suggested that topical propranolol formulation might be equally effective as systemic administration but have a better safety profile.

#### Safety and efficacy of propranolol 0.1% eye micro-drops in newborns

Recently an open-label, trial was performed to evaluate the safety and efficacy of propranolol 0.1% eye micro-drops in preterm newborns with stage 2 ROP without plus [64]. The study was planned according to the Simon optimal two-stage design for phase II clinical trials and it was discontinued before starting the second stage since the number of failures was above the set threshold. Even though the objective to move to the second stage was not reached, the percentage of ROP progression (around 26%) was substantially similar to that obtained after oral propranolol administration. Nevertheless, no adverse effects were observed and propranolol plasma levels were significantly lower than those measured after oral administration (consistently below the cut-off value of 20 ng/mL). Therefore, treatment with propranolol 0.1% eye micro-drops seems to be safe and well tolerated in preterm newborns, but not sufficiently effective in reducing ROP progression.

Further research is then required to identify the optimal dose and schedule of topical propranolol therapy for ROP.

### Research hypothesis

The present open-label trial is planned to evaluate safety and efficacy of propranolol 0.2% eye micro-drops in preterm newborns with stage 1 ROP without plus.

### Study objectives

#### Primary objective

To evaluate the safety and efficacy of propranolol 0.2% eye micro-drops in preventing ROP progression from Stage 1 without plus to Stage 2 with plus or 3 with plus and therefore in reducing the rate of laser treatment and rescue treatment with bevacizumab.

#### Secondary objective

To analyze the efficacy of propranolol 0.2% eye micro-drops in preventing ROP progression from Stage 1 without plus to more severe Stage ROP.

### Trial design

The present study is a multicenter, open-label, single arm phase II trial planned as a Simon optimal two-stage design [65], under the hypothesis that the treatment decreases the incidence of ROP progression to stage 3 with plus (estimated from historical data to be at least 19%) by 50% or more.

## Methods: Participants, interventions, outcomes

### Study setting

Preterm newborns delivered at GA ranging from 23 to 32 weeks and admitted to the neonatal intensive care units (NICU) contributing to the study (1. Meyer University Children’s Hospital in Florence; 2. Institute of Pediatrics and Neonatology, Fondazione IRCCS Ospedale Maggiore Policlinico, Mangiagalli e Regina Elena, Università di Milano; 3. San Gerardo Hospital in Monza; 4. University Hospital Policlinico Santa Maria alle Scotte, Siena; 5. University Hospital in Varese; 6. Children’s Hospital Spedali Civili in Brescia) were considered for enrolment.

### Inclusion criteria

The following inclusion criteria were considered:Preterm newborns (GA 23–32 weeks) with birth weight < 1500 g diagnosed with stage 1 ROP in zone II or III, without plus;A signed informed consent from parents.

### Exclusion criteria

Newborns with heart failure, congenital cardiovascular anomalies except for persistent ductus arteriosus, patent foramen ovale and small ventricular septal defects, recurrent bradycardia (heart rate < 90 beat per minute), second or third degree atrio-ventricular block, intractable hypotension, renal failure, current cerebral hemorrhage, other diseases which contraindicate the use of β-AR blockers.Newborns with ROP at a more advanced stage than stage 1.Newborns with aggressive posterior ROP (AP-ROP).

### Intervention

All enrolled newborns will receive propranolol as ophthalmic solution (0.2%). Three micro-drops of 6 μL propranolol solution (= 6 μg propranolol/μ-drops) will be topically applied four times daily (every 6 h) in each eye with a calibrated pipette. After propranolol administration, the nasolacrimal duct will be carefully compressed for 1 min in order to decrease the percentage of drug absorbed by the conjunctival and nasal vessels. The treatment will be started as soon as the diagnosis of stage 1 ROP without plus is confirmed and will be continued until the complete development of retinal vascularization, but for no longer than 90 days. However, ophthalmologic exams will also be performed after this period to exclude possible rebound phenomenon. In these cases, propranolol eye micro-drops treatment will be resumed until retinal vascularization is completed.

The ophthalmologic approach for newborns enrolled in the study will be in accordance with the guidelines adopted by the ETROP Cooperative Group and the AAP/AAO/AAPOS guidelines [3, 66, 67]. The RetCam Imaging System will be systematically used by ophthalmologists to evaluate ROP evolution.

Eye drops will be prepared sterilely by diluting propranolol hydrochloride powder (ACEF, Fiorenzuola d’Arda, Piacenza, Italy), in sterile water for injection at a concentration of 2%. Then, the propranolol 0.2% solution will be obtained in a horizontal laminar flow hood adding 9 ml of saline solution to 1 ml of propranolol 2% preparation.

Newborns with ROP who progressed to stage 2 plus or stage 3 plus will be treated with laser photocoagulation or intravitreal anti-VEGF (bevacizumab) administration. The ophthalmologists will choose the treatment they will consider most appropriate.

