## Discussion

The aim of the present study is to evaluate the therapeutic role of propranolol 0.2% eye micro-drops in newborns with a precocious stage of ROP. Treatment with oral propranolol is effective in preventing ROP progression in preterm newborns, but appears unsafe. Furthermore, data from a previous trial suggested that propranolol 0.1% eye micro-drops had an optimal safety and tolerability profile in preterm newborns, although efficacy in reducing ROP progression was not sufficient. The optimal dosage and concentration of propranolol eye drops to use in preterm newborns are still uncertain. However, considering the optimal safety profile of propranolol 0.1% eye micro-drops, it is likely that this dosage could be increased without compromising safety. Similarly, the excellent local tolerability also suggests that the concentration of propranolol solution could be increased without the risk of local adverse reactions. According to these considerations, the present protocol study plans to increase both dosage and concentration of propranolol eye drops in order to improve the efficacy profile. Additionally, the optimal time to start propranolol treatment has not yet been clarified. In the previous study with 0.1% eye micro-drops, the treatment was started at an advanced stage of ROP (stage 2 without plus), a stage that is quite close to the threshold of ophthalmological treatment. Therefore, we assumed that starting therapy at an earlier stage of ROP (stage 1) could represent an additional advantage.

Finding the optimal dosage and schedule of propranolol eye micro-drops treatment could represent a crucial turning point in ROP therapy. In fact, propranolol eye drops is apparently a safe, inexpensive and easily affordable treatment. Considering also the high prevalence of ROP registered in middle income countries, these advantages become even more relevant.

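### The stated drug mass per micro-drop (6 μg) is half of what the stated concentration and drop volume give (12 μg), so the three dose figures cannot all be right

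*Protocol article*

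**What the plan says.** The Intervention section of the protocol article gives the dose in several parts:

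- **Concentration:** a 0.2% ophthalmic solution. The title, abstract and objectives use the same figure.
- **Volume and number of drops:** "Three micro-drops of 6 μL propranolol solution".
- **Mass per drop:** in brackets, "propranolol solution (= 6 μg propranolol/μ-drops) will be topically applied four times daily".
- **Frequency:** "four times daily (every 6 h) in each eye with a calibrated pipette".
- **Preparation:** a 2% stock is made from propranolol hydrochloride powder. The study solution is then obtained by "adding 9 ml of saline solution to 1 ml of propranolol 2% preparation".

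The section on stop criteria and dose changes repeats the 6 μL volume and the 0.2% concentration for a possible restart with two drops instead of three. It also allows a restart at up to 0.3%. It gives no mass. The bracketed 6 μg is the only drug mass per drop in the article, and nothing explains how it was obtained.

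**The concern.** One sentence ties a drop volume to a drug mass, and the sentence before it fixes the concentration. Any two of these figures determine the third, and the third as printed does not agree.

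This is the definition of the investigational treatment in preterm newborns, so it matters more than a slip in background text. The safety argument rests on systemic exposure: mean plasma propranolol is judged against 20 ng/mL, a value taken from experience with oral dosing at 1 mg/kg/day. Anyone who relates measured plasma levels to the nominal dose, or expresses that dose per kilogram, gets answers that differ two-fold depending on which figures they start from.

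**Working it through.** **Inputs, all from the Intervention section:** concentration 0.2%; drop volume 6 μL; stated mass 6 μg per drop; 3 drops per eye per administration; 4 administrations a day; 2 eyes; stock 2%; dilution 1 mL of stock plus 9 mL of saline. Percentages are read as weight per volume, so 1% = 10 mg/mL = 10 μg/μL.

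**Step 1. Concentration.**
- From the label: 0.2 × 10 = 2 μg/μL.
- From the recipe: 20 μg/μL × 1 mL / (1 + 9) mL = 2 μg/μL.
- The two agree.

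**Step 2. Mass per drop.** Mass = volume × concentration = 6 μL × 2 μg/μL = 12 μg. The stated figure is 6 μg, and 12 / 6 = 2.

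**Step 3. Attempts to reproduce 6 μg.**

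| Reading | Mass per drop | Agrees with the other stated figures? |
|---|---|---|
| 6 μL at 0.2% | 12 μg | Yes, but not with 6 μg |
| Three drops totalling 6 μL (2 μL each) at 0.2% | 4 μg | Does not give 6 μg |
| 6 μL at 0.2%, as base rather than salt (assumed factor about 0.88, not in the article) | about 10.5 μg | Does not give 6 μg |
| 6 μL at 0.1% | 6 μg | Contradicts the concentration |
| 3 μL at 0.2% | 6 μg | Contradicts the drop volume |

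The salt-to-base result does not depend on the exact factor assumed: only a factor of 0.5 would give 6 μg. Rounding cannot produce a factor of exactly 2.

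**Step 4. Daily nominal dose.** Drops per day = 3 × 4 × 2 = 24.

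| | By concentration and volume | By stated mass |
|---|---|---|
| Per drop | 12 μg | 6 μg |
| Per eye per administration (3 drops) | 36 μg | 18 μg |
| Per day, both eyes (24 drops) | 288 μg | 144 μg |

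**Step 5. Scale per kilogram.** This is an illustration only. It assumes a weight of 843 g, the mean birth weight of the historical infants with stage 1 ROP at first visit (Table 1); weight during treatment will differ. Then 288 / 0.843 ≈ 342 μg/kg/day and 144 / 0.843 ≈ 171 μg/kg/day. The ratio is 2 at any weight.

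**Step 6. Dose-change rules.** Going from three drops to two multiplies the dose by 2/3 on either basis: 16 drops a day give 192 instead of 288 μg, or 96 instead of 144 μg. The rule is written in drops, volume and concentration, and the possible increase is written in concentration. Neither uses the mass.

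**The case against.** The best defence is that the working instruction is coherent without the bracket. Concentration, drop volume, drop count, frequency and dilution recipe agree with one another and with the dose-change section. Drops are prepared by dilution and given by calibrated pipette, and no step in the article is carried out from the mass. The 6 μg appears once, as an equivalence. The article condenses a fuller protocol, so the slip may exist only here.

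Most of this stands, and it limits what a reader may infer:

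- **That infants would receive the wrong dose.** Not shown. Drops prepared and pipetted as described would contain 12 μg by arithmetic, and nothing tells staff to dose from the mass.
- **That the plasma-concentration endpoint is distorted.** Not supported. Propranolol is assayed on dried blood spots and its mean compared with 20 ng/mL; it is not calculated from the nominal dose.
- **That the restart rules are affected.** They are not, because they state no mass.
- **That a comparison with the earlier 0.1% drops or with oral dosing is wrong.** The article makes no such comparison by mass, and it gives no drop volume or drop count for the earlier trial.
- **That 6 μg was carried over from the 0.1% trial.** The figure would fit 6 μL at 0.1%, but the article does not show its origin. The Discussion's statement that "the present protocol study plans to increase both dosage and concentration of propranolol eye drops" settles nothing about the mass per drop.

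The defence does not remove the contradiction. All three figures are printed in the current text, and no reading reconciles them.

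**Conclusion.** The point holds as an internal contradiction in the stated dose. By the article's own concentration, volume and recipe a micro-drop contains 12 μg, and the article says 6 μg. The gap is exactly two-fold: 288 against 144 μg a day over 24 drops. The only assumption needed is the usual weight-per-volume reading of the percentage, which applies to both the stock and the diluted solution.

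The effect is confined to the nominal dose and to any exposure per μg or per kg derived from it. No endpoint, sample size, stopping boundary or decision rule changes. It should still be corrected, because it sits in the text that defines an investigational treatment for preterm newborns. Which of the figures is intended cannot be settled from the article, and this review does not say.

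**What to change.** The sponsor should check concentration, drop volume and mass per drop in the Intervention section against the pipette calibration and the pharmacy preparation record, and then state one set in which mass equals volume times concentration. Any other trial document that repeats the mass per drop should be checked at the same time; whether any does cannot be seen from the article. If a nominal dose per kilogram is ever reported, it should be derived from the reconciled set. The dose-change section contains no mass and needs no correction on this account beyond staying consistent with the reconciled volume and concentration.

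The cost is a text correction and a records check. The design, sample size and analysis are unaffected.
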